## Abstract

**Background:**

There is widespread agreement that the integration of cessation services in lung cancer screening (LCS) is essential for achieving the full benefits of LCS with low-dose computed tomography (LDCT). There is a formidable knowledge gap about how to best design feasible, effective, and scalable cessation services in LCS facilities. A collective of NCI-funded clinical trials addressing this gap is the Smoking Cessation at Lung Examination (SCALE) Collaboration.

**Methods:**

The Cessation and Screening to Save Lives (CASTL) trial seeks to advance knowledge about the reach, effectiveness, and implementation of tobacco treatment in lung cancer screening. We describe the rationale, design, evaluation plan, and interventions tested in this multiphase optimization strategy trial (MOST). A total of 1152 screening-eligible current smokers are being recruited from 18 LCS sites (*n* = 64/site) in both academic and community settings across the USA. Participants receive enhanced standard care (cessation advice and referral to the national Quitline) and are randomized to receive additional tobacco treatment components (motivational counseling, nicotine replacement patches/lozenges, message framing). The primary outcome is biochemically validated, abstinence at 6 months follow-up. Secondary outcomes are self-reported smoking abstinence, quit attempts, and smoking reduction at 3 and 6 months. Guided by the Implementation Outcomes Framework (IOF), our evaluation includes measurement of implementation processes (reach, fidelity, acceptability, appropriateness, sustainability, and cost).

**Conclusion:**

We will identify effective treatment components for delivery by LCS sites. The findings will guide the assembly of an optimized smoking cessation package that achieves superior cessation outcomes. Future trials can examine the strategies for wider implementation of tobacco treatment in LDCT-LCS sites.

**Trial registration:**

ClinicalTrials.gov
NCT03315910

## Introduction

In response to the landmark National Lung Screening Trial [1], the United States Preventive Services Task Force [2] (USPSTF) recommends annual low-dose computed tomography lung cancer screening (LDCT-LCS) for high-risk individuals (adults 55–80 years of age with 30 pack per year smoking history who currently smoke or have quit within the past 15 years). These guidelines were revised in 2021 such that adults aged 50–80 years with a 20-pack-year smoking history who currently smoke or quit within the past 15 years are now recommended for LDCT-LCS [3]. There are an estimated 14.5 million Americans eligible for screening and approximately 50% are likely people who currently smoke [4].

LDCT-LCS provides an unprecedented opportunity to further reduce tobacco-related morbidity and mortality by delivering smoking cessation treatment within the context of lung cancer screening [5, 6]. There is strong support for the integration of tobacco treatment as an indicator of high-quality LCS [7] and the cost-effectiveness of LDCT-LCS is enhanced when paired with tobacco cessation counseling [8, 9].

Although clinical practice guidelines for the treatment of tobacco use and dependence exist [10], access to and utilization of tobacco treatment services within the context of LCS has been highly variable [11]. Little is known about the readiness and capacity of LCS sites to deliver evidence-based tobacco treatment. There is also a knowledge gap in identifying the reach, effectiveness, implementation and sustainability of various treatment approaches [12]. Studies that have examined the effectiveness of providing only brief cessation advice and/or brief cessation interventions (i.e., brochure, brief counseling, Quitline referral) have generally been under-powered and failed to produce significant findings [13–15]. For LDCT-LCS sites to integrate tobacco treatment into their screening protocols, it is also critical to understand implementation costs and workflows [6]. Although a simulation-based cost-utility analysis strongly supports the value of smoking cessation [16], the incremental costs of delivering treatment within LDCT-LCS are largely unknown. Finally, in order to mitigate tobacco-related disparities, it is essential to reach and engage people who smoke from diverse racial and ethnic backgrounds in tobacco treatment [17]. Recruiting diverse populations of people with smoking histories in tobacco cessation trials is often challenging, particularly for the engagement of Black people who smoke [18].

Eight (8) projects were awarded National Cancer Institute (NCI) grants in response to RFA #15-011, and the teams of these projects have formed the SCALE Collaboration, coordinated by the NCI [19]. As one of the SCALE studies, the Cessation and Screening to Save Lives (CASTL) trial was designed to advance the science of tobacco treatment effectiveness and implementation in the LCS context. Here, we present the study design, tobacco treatment protocols, and evaluation plan of the CASTL trial, including an ancillary investigation focusing on the understanding of recruitment and engagement of Black people seeking LDCT-LCS in tobacco treatment.

## Methods

### Overview of CASTL study design

The CASTL Project utilizes a multiphase optimization strategy trial (MOST) [20] conducted at 18 lung cancer screening sites located across the USA. The MOST methodology leverages a full-factorial or a fractional-factorial design to systematically and efficiently evaluate the effects of individual treatment components and their interactions and then select those that produce the most favorable net effects [20–22]. The MOST enables participants to be randomized into one of 16 combinations of intervention components, stratified by participating site. The study design is depicted in Fig. 1. All participants receive enhanced standard care (i.e., cessation advice and referral to the national Quitline) and are randomly assigned to receive additional tobacco treatment components alone or in combination (i.e., motivational counseling, nicotine replacement patch, nicotine replacement lozenges, message framing booster). This factorial design enables the estimation of the main effect contribution of each of the four treatment components and interactions between components [23, 24]. Each screening site is managed by one or more site coordinators (SC). Each of the 18 participating sites is expected to recruit 64 patients who smoke and are eligible for lung cancer screening with LDCT (total target *N* = 1152). Surveys and qualitative interviews are being conducted with participating patients and staff. The primary outcome is biochemically validated, smoking abstinence at 6 months follow-up. Secondary cessation outcomes are self-reported smoking abstinence, quit attempts, and smoking reduction at 3- and 6-month follow-up. Guided by Proctor’s Implementation Outcomes Framework (IOF) [25], our evaluation plan includes measurement of implementation process outcomes including the treatment’s reach of the target population, fidelity, acceptability, appropriateness, sustainability, and cost.

**Fig. 1 Fig1:**
[figure not shown]
Study design

### Study aims

#### Aim 1

To identify which of four evidence-based tobacco treatment components contribute to superior cessation endpoints among people who currently smoke and are seeking lung cancer screening over and above enhanced standard care (i.e., minimum intervention needed for change). The four tobacco treatment components being tested are (1) motivational interviewing (MI) (yes vs. no), (2) nicotine replacement therapy (NRT) patch (yes vs. no), (3) NRT lozenge (yes vs. no), and (4) message framing (gain vs. loss). We hypothesize that all four treatment component enhancements will be statistically superior to enhanced standard care alone and that some synergistic treatment component effects will emerge. For the message framing condition, we expect that gain-framed messages will result in higher quit rates. The primary cessation outcome is biochemically verified 7-day point abstinence at 6 months following study enrollment. Secondary cessation outcomes are self-reported 7-day point prevalence abstinence at 3 months, continuous abstinence (between the date of randomization and date of completion of follow-up surveys) at 3 and 6 months, and self-reported 24-h quit attempt at 3 and 6 months.

#### Aim 2

To estimate the cost and incremental cost-effectiveness of evidence-based tobacco treatment components, delivered alone and in combination.

#### Aim 3

To conduct a robust, mixed methods evaluation of the implementation process and assess site characteristics and organizational factors that may influence the implementation of tobacco treatment in lung cancer screening settings.

#### Aim 4

To analyze whether lung cancer screening results (i.e., Lung-RADS®) moderate smoking abstinence outcomes. We hypothesize that participants found to have one or more screening abnormalities will be more likely to quit smoking and maintain smoking abstinence.

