### Patient randomization and assignment to treatment group

Eligible patients who smoke are registered via MSK’s Clinical Trials Management System to the CASTL trial and randomized using the Clinical Research Database by a CRC. Individual study participants are randomized to one of the 16 intervention combinations listed in Table 1. Randomization is stratified using the method of the random permuted block by participating LDCT-LCS site. After patient registration and randomization, a designated MSK CRC sends each SC a secure email containing the patient’s treatment assignment.

**Table 1 Tab1:** Treatment components

Components					
Conditions	Enhanced standard care	Motivational interviewing	NRT lozenge	NRT patch	Message framing
**1**	Yes	Yes	No	No	Loss
**2**	Yes	Yes	No	No	Gain
**3**	Yes	Yes	No	Yes	Loss
**4**	Yes	Yes	No	Yes	Gain
**5**	Yes	Yes	Yes	No	Loss
**6**	Yes	Yes	Yes	No	Gain
**7**	Yes	Yes	Yes	Yes	Loss
**8**	Yes	Yes	Yes	Yes	Gain
**9**	Yes	No	No	No	Loss
**10**	Yes	No	No	No	Gain
**11**	Yes	No	No	Yes	Loss
**12**	Yes	No	No	Yes	Gain
**13**	Yes	No	Yes	No	Loss
**14**	Yes	No	Yes	No	Gain
**15**	Yes	No	Yes	Yes	Loss
**16**	Yes	No	Yes	Yes	Gain

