#### Tobacco treatment components

Careful attention was given to the selection of tobacco treatment components guided by the following principles: (a) evidence-based, (b) feasible and scalable for high and low resource LDCT-LCS sites, and (c) sustainable beyond the CASTL study period. The study is designed to compare enhanced standard care (control group) with four tobacco treatment components: (1) motivational interviewing (MI) (yes vs. no), (2) nicotine replacement therapy (NRT) patch (yes vs. no), (3) NRT lozenge (yes vs. no), and (4) message framing (gain vs. loss).

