##### Message framing

Prior research has demonstrated that gain-framed messages (i.e., emphasize the benefits of quitting) may be more effective than loss-framed (i.e., emphasize the risks of persistent smoking) or non-framed (neutral) messages for encouraging smoking cessation [33, 34]. Within 1 month of receiving their LDCT-LCS results, participants receive a standardized message that emphasizes either the benefits of quitting (gain-framed) or the risks of continuing to smoke (loss-framed). Audio and video messages are pre-recorded by SCs and sent by email. For patients who do not have an email address, messages are sent via letter. A manipulation check assessing participant comprehension of the message framing intervention component is conducted.

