## Discussion

Lung cancer screening provides a unique opportunity to engage current tobacco users in cessation efforts. Integration of effective evidence-based tobacco use treatment methods may increase the benefits of LDCT-LCS, ultimately improving health outcomes in an older population of people who smoke. This paper describes the CASTL clinical trial using the MOST factorial design to test the effectiveness of several tobacco treatment interventions under investigation including referrals to the national Quitline, nicotine replacement therapy (patch and lozenge), motivational counseling, and message framing delivered to patients seeking lung cancer screening at LDCT-LCS sites nationwide.

Using a hybrid type II trial design [75], we will generate data to support the selection of an optimal combination of tobacco use treatment interventions for patients undergoing LCS while explicitly collecting data on implementation processes (e.g., patient and provider satisfaction, fidelity, cost) to facilitate subsequent dissemination and implementation efforts. The main deliverable in this trial will be the optimal intervention components. More specifically, if, hypothetically speaking, intervention combinations 3, 4, 7, and 8 in Table 1 yield the highest abstinence rates, then the optimal intervention would involve a synergic effect between motivational interviewing and nicotine patch in addition to enhanced standard care. This determination will have to be made empirically, after the trial has concluded and data analyzed.

Our comprehensive evaluation of both effectiveness and contextual aspects of implementation across a diverse group of LDCT-LCS settings will inform LDCT-LCS program decisions about necessary organizational structures, resources, and processes needed to integrate tobacco dependence treatment. Given the diversity of current cessation practices in the LDCT-LCS setting, this comprehensive approach will allow for the most robust data to inform implementation practices across different program sizes, geographic regions, academic affiliations, and other LDCT-LCS program characteristics.

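### No condition is enhanced standard care alone, so framing can be tested only as gain versus loss, and top rates in the MI-plus-patch conditions would not by themselves show synergy

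*Protocol article*

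**What the plan says.** **Hypothesis and comparator.** Study aims, Aim 1, says: "We hypothesize that all four treatment component enhancements will be statistically superior to enhanced standard care alone". The section Tobacco treatment components repeats the comparator: "The study is designed to compare enhanced standard care (control group) with four tobacco treatment components". Both sections define MI, patch and lozenge as yes versus no, and framing as gain versus loss. The sentence after the Aim 1 hypothesis says of framing that "we expect that gain-framed messages will result in higher quit rates".

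**Allocation.** Under Patient randomization and assignment to treatment group, "Individual study participants are randomized to one of the 16 intervention combinations listed in Table 1". In that table the framing column holds only Loss or Gain. The section Message framing agrees: "participants receive a standardized message that emphasizes either the benefits of quitting (gain-framed) or the risks of continuing to smoke (loss-framed").

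**Synergy.** The Discussion describes the main deliverable with a hypothetical. If conditions 3, 4, 7 and 8 "yield the highest abstinence rates, then the optimal intervention would involve a synergic effect between motivational interviewing and nicotine patch". It then says that the determination will be made empirically after the trial.

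**Analysis.** The Aim 1 part of Data analysis specifies a saturated logit mixed model with four main effects and 11 interactions. Terms with p < 0.05 in the type 3 table are retained, and selection is generally guided by Benjamini-Yekutieli adjusted p-values. The section treats synergistic effects and interactions as the same thing and forecasts that those that emerge will form the optimized package. The Overview of the design says instead that components and their interactions are evaluated together and chosen for their net effect.

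**The concern.** Two statements about what the trial can conclude do not follow from its design.

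The first is the claim that all four components will beat enhanced standard care alone. With no message-free condition, a significant gain-versus-loss result could be reported as superiority of framing over standard care. Gain could beat loss and still be no better than sending no message.

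The second is the reading of the deliverable. If the MI-plus-patch conditions come out on top, the Discussion would call that synergy. Two components that each work, and do not interact at all, give the same ranking. The final report could then describe additive benefit as synergy, which is a different claim about how the package works.

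**Working it through.** **1. Reproducing the article's own figures.** These inputs come from the section on statistical power and sample size.

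- Attrition of 20% leaves 1152 × 0.8 / 2 = 460.8 participants per factor level. Two-sided power at 0.20 SD and 5% is then 85.9%, against the stated 85%.
- Arcsine effect for 20% versus 12%: 2·asin(√0.20) − 2·asin(√0.12) = 0.2198, against the stated 0.22.

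Both agree. They concern main effects (one factor level against the other), and nothing below disputes them.

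**2. Is there a standard-care-alone condition?** Reading Table 1 row by row:

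- Conditions with no framed message: 0 of 16.
- Conditions with no MI, lozenge or patch: 9 (Loss) and 10 (Gain). Both are standard care plus a message.

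In model terms, take an intercept for standard care alone and separate effects for MI, lozenge, patch, gain and loss. That is six columns. In every row gain + loss = 1, which equals the intercept column, so the rank is 5. Gain minus loss is estimable. Gain against no message, and loss against no message, are not, at any sample size. The effects of MI, lozenge and patch remain estimable on a background that always includes a message.

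**3. Does the ranking in the Discussion imply synergy?** In Table 1, conditions 3, 4, 7 and 8 are all, and only, those with MI = Yes and patch = Yes.

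Assumption for illustration: base abstinence 12%, and MI and patch each raising it to 20% when given without the other. Both rates are from the article's power illustration; applying them to each component is mine. Lozenge and framing effects are set to zero.

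- Base odds: 0.12/0.88 = 0.1364.
- Odds ratio for each component: (0.20/0.80)/(0.12/0.88) = 1.833.
- Both components, no logit interaction: odds 0.1364 × 1.833² = 0.4583, so the rate is 0.4583/1.4583 = 31.4%.
- Both components, with an antagonistic interaction of minus half a main effect on the logit scale: odds 0.4583/√1.833 = 0.3385, so the rate is 25.3%.
- Both components, additive risks: 12 + 8 + 8 = 28%.

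| Scenario | Neither | MI only | Patch only | Both (3, 4, 7, 8) |
|---|---|---|---|---|
| No interaction, logit scale | 12% | 20% | 20% | 31.4% |
| Additive risks | 12% | 20% | 20% | 28% |
| Antagonistic, logit scale | 12% | 20% | 20% | 25.3% |

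The four conditions rank highest in expectation in every row, including the one where the components work against each other.

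If lozenge and framing also have effects, then with no interactions the four conditions remain the top four as long as the smaller of the MI and patch effects exceeds the lozenge and framing effects added together (logit scale).

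**4. Observed rather than expected rates.** With 1152/16 = 72 per condition and the no-interaction scenario, 200,000 simulated trials with ties broken at random put exactly these four conditions in the observed top four in 42% of trials. With the antagonistic interaction the share is 6%.

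**The case against.** Much of the plan already says the right thing.

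- **Framing.** The gain-versus-loss expectation stands in the sentence after the disputed hypothesis, and the factor is defined that way throughout. A reader might infer that the framing test is undefined. It is not; what fails is the broader claim about standard care and the control-group label.
- **Other components.** A reader might also infer that MI, patch and lozenge cannot be evaluated. They can, each as yes versus no, provided that the background is named.
- **Costs.** Aim 2 does not specify a contrast of framing with no message, and the cost of delivering a message can still be estimated. Only its effect against no message is out of reach.
- **Synergy.** The Discussion sentence is openly hypothetical and defers to the data. A reader might infer that the trial would declare synergy from rankings, or discard real main effects. The documents do not support that. The Aim 1 analysis tests MI by patch as a model term, guides selection by adjusted p-values and retains any reliable term, main effects included. The line about interactions forming the package is worded as a forecast.
- **Frequency.** The additive example does not make the Discussion's event near-certain in observed data: 42% in the scenario above, and dependent on the assumed rates.

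All of this limits the point to wording. It does not rescue the two statements. The hypothesis still names a comparator that no participant receives, and the worked example still reads synergy from a ranking when the analysis section equates synergy with interaction.

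**Conclusion.** The point holds as a wording fault in two places.

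For framing, the absence of a standard-care-alone condition is a fact of Table 1 (0 of 16) and rests on no assumption. Superiority of framing over standard care cannot be shown. The other three components can be shown only to add to standard care plus a framed message.

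For synergy, the inference in the Discussion is invalid and inconsistent with the analysis section. The figures of 12%, 20%, 20% and 31.4% are illustrative, but the logic does not depend on them: two positive effects with no interaction put the combined conditions first on average over the other factors. The practical damage is limited, because MI and patch would both belong in the package under that ranking anyway. What would be wrong is the label of synergy.

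No planned test, sample size or randomization is affected. The correction should be made before the analysis begins, which the article places after data collection ends.

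**What to change.** 1. **Study aims (Aim 1) and Tobacco treatment components.** State the hypothesis as MI, patch and lozenge each yes versus no, averaged over the other factors, with enhanced standard care plus a framed message as the reference. State framing as gain versus loss only. Remove the claim that it is superior to standard care alone.
2. **Discussion.** Replace the ranking of conditions 3, 4, 7 and 8 with a criterion: MI-patch synergy is claimed only if the MI-by-patch interaction is positive on the model's logit scale and passes the Benjamini-Yekutieli rule already planned. Naming the scale matters. The additive-risk row above corresponds to an interaction odds ratio of (0.28/0.72 × 0.12/0.88)/(0.20/0.80)² = 0.85, which is negative on the logit scale.
3. **Data analysis, Aim 1.** Reword the sentence on interactions forming the optimized package so that retained main effects also enter it, in line with the net-effect principle in the Overview.

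The cost is wording, plus one claim given up: that framing beats enhanced standard care.

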#### Cost

The economic impact of the tobacco treatment components will be assessed by performing both cost and cost-effectiveness analysis. The goal of the cost analysis is to estimate the incremental costs associated with delivering tobacco treatment components in the context of LDCT-LCS. The primary endpoint of this analysis is the cost of each treatment component and the cost of each permutation of treatment components. The base-case cost analysis includes the costs of all resources consumed for the implementation and delivery of the tobacco treatment components. We will also examine costs and potential payment sources (e.g., health insurance benefits) from the provider (i.e., LDCT-LCS site) perspective, in order to estimate the net cost to screening sites that want to adopt the optimized treatment combination or individual components of it. Data sources for the cost analysis include SC treatment logs which document the delivery of treatment components and associated personnel time. Administrative and overhead costs will be estimated by each study site. The cost of medications (nicotine lozenges and patches) will be based on acquisition costs. In sensitivity analysis, we will examine a range of unit cost values for these items, reflecting the range of values reported in the medical literature and on pharmacy websites. Intervention cost estimates will include only the resources used in implementing and delivering the study interventions. Resources used solely for research purposes will be excluded.

Cost-effectiveness will be estimated as the incremental cost per additional participant with biochemically verified abstinence. This endpoint corresponds with the trial’s primary clinical endpoint and will facilitate comparison with other smoking cessation trials that estimate cost-effectiveness as cost per quit [61]. In addition to intervention costs, the numerator of the cost-effectiveness ratio will include the costs of smoking cessation supplies consumed after the study treatment period and other non-study tobacco treatment services received and the patient time and travel costs associated with these services. The use of additional tobacco treatments and time and travel costs will be reported by participants in the 3- and 6-month follow-up surveys. Incremental cost-effectiveness ratios will be estimated for all non-dominated intervention strategies, and uncertain parameters will be varied in sensitivity analysis across a range of plausible values.

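### Every condition includes a framed message, so the trial can compare gain with loss framing but cannot test whether framing adds to enhanced standard care, as Aim 1 hypothesises

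*Protocol article*

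**What the plan says.** Under Study aims, Aim 1 asks which of four components contribute "over and above enhanced standard care (i.e., minimum intervention needed for change"), and continues: "We hypothesize that all four treatment component enhancements will be statistically superior to enhanced standard care alone". The same paragraph defines the factors, with interviewing, patch and lozenge as yes versus no and framing as two frames: "3) NRT lozenge (yes vs. no), and (4) message framing (gain vs. loss"). The next sentence but one in substance narrows to framing: "For the message framing condition, we expect that gain-framed messages will result in higher quit rates".

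The section Tobacco treatment components repeats the broad comparison: "The study is designed to compare enhanced standard care (control group) with four tobacco treatment components". Enhanced standard care is described there and in the design overview as advice, print self-help material and Quitline referral. A framed message is not part of it.

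The Message framing section says that "participants receive a standardized message that emphasizes either the benefits of quitting (gain-framed) or the risks of continuing to smoke (loss-framed"). Table 1 agrees. The condition with none of the three yes/no components reads "9 Yes No No No Loss", and its partner, condition 10, differs only in having the gain message.

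For the economic aim, the Cost section says: "The primary endpoint of this analysis is the cost of each treatment component and the cost of each permutation of treatment components". It also plans incremental cost-effectiveness ratios for all non-dominated strategies.

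**The concern.** A component can be shown to add to a control only if some participants receive the control without it. Interviewing, patch and lozenge meet that condition and framing does not. The hypothesis nevertheless covers all four components and names enhanced standard care alone as the reference, which no participant receives.

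The main deliverable is a set of components to recommend to screening sites. Under the Data analysis section, model terms are kept or dropped by significance. A null framing term could be reported as framing contributing nothing, even if both messages help. A positive term could be reported as gain framing improving on enhanced standard care, even if the loss message merely did worse. A site deciding whether to send any message would have no estimate of what it gains by doing so.

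**Working it through.** **1. The plan's own power figure.** Inputs from the power section: N = 1152, 20% attrition, effect size d = 0.20, two-sided 5%. Each factor splits the sample in half, so n per level = 1152 × 0.8 / 2 = 460.8.

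Power = Φ(d × √(n/2) − 1.96) = Φ(0.20 × √230.4 − 1.96) = Φ(3.036 − 1.960) = Φ(1.076) = 85.9%, against 85% stated.

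The illustration also reproduces: 2·arcsin√0.20 − 2·arcsin√0.12 = 0.2198, stated as 0.22. The power statement is correct for a two-level main effect. For framing, that effect is gain versus loss.

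**2. Count of Table 1.** Loss: 8 conditions. Gain: 8 conditions. No message: 0 of 16. The table is otherwise a complete 2 × 2 × 2 × 2 layout.

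**3. What can be estimated.** Write one row per condition with six columns: intercept (enhanced standard care), interviewing, lozenge, patch, any message, gain versus loss.

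- The any-message column equals 1 in every row and is identical to the intercept. The matrix has rank 5 for 6 columns.
- Appending the any-message contrast raises the rank to 6, so it lies outside the row space and is not estimable.
- Appending the gain-versus-loss contrast leaves the rank at 5, so it is estimable.

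This is a property of the layout and does not depend on sample size.

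**4. What that means for interpretation.** The quit rates below are assumed, for illustration only.

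| Case | No message | Gain | Loss | Gain − loss (estimable) | Gain − none (not estimable) |
|---|---|---|---|---|---|
| A | 12% | 16% | 16% | 0 | +4 |
| B | 12% | 12% | 8% | +4 | 0 |
| C | 8% | 12% | 8% | +4 | +4 |

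In case A the framing term is zero although a message adds 4 points. Cases B and C give identical trial data, yet gain framing adds nothing in B and 4 points in C.

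**5. The other three components.** Each has 8 yes and 8 no conditions, balanced over frame, so their effects are estimable. Their background is enhanced standard care plus a message, not enhanced standard care alone.

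**6. The worked example in the Discussion.** It supposes that conditions 3, 4, 7 and 8 do best and describes the package as interviewing and patch on top of enhanced standard care. In Table 1, conditions 3 and 7 carry the loss message and conditions 4 and 8 the gain message. The described package leaves out something that every participant in those cells is assigned to receive.

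**7. Aim 2.** The cost of delivering a message can be tallied without a no-message arm. The incremental ratio for adding a message is (cost with − cost without) / (quit rate with − quit rate without). No participant supplies the quit rate without a message. Gain versus loss can be compared.

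**The case against.** The strongest reply is that the article already states the testable hypothesis. It labels framing as gain versus loss wherever it lists the factors, and it says in Aim 1 that gain is expected to do better. On that reading, the framing sentence specifies what the general hypothesis means for the one factor without a no level. No planned analysis attempts message versus no message: the model fits the Table 1 factors, and power is stated for their main effects. Comparing two frames is a legitimate question.

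Most of this stands. The gain-versus-loss contrast is declared, valid and covered by the stated power at the planned number. But the framing sentence does not withdraw the claim for all four components. The Tobacco treatment components section repeats the broad comparison, and the Discussion example describes a package without the message. A statistical analysis plan could not supply the missing contrast.

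A reader might also infer that the 16 strategies form gain/loss pairs of equal cost, so that the member of each pair with the lower observed quit rate is automatically dominated. The documents do not support that. The Cost section and the Aim 2 analysis text put later cessation supplies, other tobacco treatment services, and patient time and travel into the numerator. These can differ by frame, and no message costs are given. Nor does it follow that the 16 strategies should be pooled into 8 over frame. That would discard the gain-versus-loss economic comparison and average over framing interactions that the plan intends to examine.

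**Conclusion.** The point holds as a mismatch between a stated hypothesis and the design. For one of the four components, superiority over enhanced standard care cannot be estimated at any sample size, because 0 of 16 conditions omit the message. This rests on Table 1 and the Message framing section. Figure 1 is not visible in the text reviewed, but those two places are enough to settle it. The quit rates in cases A to C are assumptions and only show the direction of possible misreadings.

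A reader might infer that the framing factor is wasted or the factorial design invalid. Neither follows. Gain versus loss is a proper randomised contrast, and the yes/no effects of interviewing, patch and lozenge stand once their background is described correctly. The 85% power applies at 1152 participants. The Trial status section says that number will not be reached, which is a separate matter.

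**What to change.** - **Study aims (Aim 1) and Tobacco treatment components:** limit the claim of superiority over enhanced standard care to interviewing, patch and lozenge. State the framing hypothesis only as gain versus loss.
- **Same places:** state that a framed message is part of the background in every condition, so the reference for the three yes/no components is enhanced standard care plus a framed message.
- **Discussion:** include the message whenever the optimised package is described, including in the worked example.
- **Cost section and Aim 2 analysis:** state that the delivery cost of a message can be reported, that its incremental cost per quit over enhanced standard care cannot be estimated, and that only gain versus loss can be compared. Keep all 16 strategies.

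The cost is a few sentences. No arm, sample size or model changes, and the article places analysis after data collection ends. The sponsor gives up only a claim that the design cannot support. No new arm is proposed. For scale, a three-level framing factor (none, gain, loss) at the planned number would leave 1152 × 0.8 / 3 = 307.2 per level and 69.8% power for each pairwise comparison at d = 0.20.
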